### Design and setting

2.1

This is a randomized, multicentre clinical trial with 2 parallel groups. The study will be conducted in a primary care setting. The Research Unit group from La Alamedilla Health Center, Biomedical Research Institute of Salamanca (IBSAL), will coordinate the project on 5 sites from the Network for Preventive Activity and Health Promotion (REDIAPP) (Salamanca, Valladolid, Cuenca, Palma de Mallorca, and Zaragoza).

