### Randomization

2.4

Participants will be randomly assigned to either the IG or the CG. Randomization will be performed after informed consent is obtained. The allocation sequence will be generated through a standardized computer programme (Epidat 4.2)^[41]^ by an independent researcher and concealed until the trial arms are assigned.

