#### Pro-Inflammatory markers

2.6.7

A centralized laboratory will measure levels of IL-1β, IL-7, and adiponectin, as they are considered pro-inflammatory markers related to obesity.^[55]^ Venous blood sampling will be performed between 8:00 am and 9:00 am after participants have fasted and abstained from smoking, consumption of alcohol, and caffeinated beverages for 12 hours. Other laboratory determinations, such as plasma glucose, creatinine, total serum cholesterol, high-density lipoprotein (HDL) cholesterol, low-density lipoprotein (LDL) cholesterol, and triglyceride concentrations will be determined using standard automated enzymatic methods. Glycosylated hemoglobin, high-sensitivity C-reactive protein levels, insulinemia, and fibrinogen values will be measured with an immune-turbidimetric assay. An ELISA will be used to determine the levels of thyroid-stimulating hormone (TSH) and free T4 hormone. Spot morning urine samples will be collected to determine the albumin–creatinine ratio. The analyses will be performed at the hospitals in the cities participating in external quality assurance programs of the Spanish Society of Clinical Chemistry and Molecular Pathology.

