### Analysis of intervention effect in primary and secondary outcomes

2.9

To analyze the changes, at 3 and 12 months from baseline, in primary (weight loss) and secondary endpoints within the same group, we will use the paired *t* test or McNemar test for quantitative or dichotomy variables, respectively.

To analyze the effect of the intervention, we will compare the changes from baseline observed between the IG and CG in weight (primary endpoint) and secondary endpoints, using ANCOVA at 3 and 12 months, adjusting for baseline measures of each variable.

In order to analyze the group effect in the follow-up for primary and secondary endpoints, we will perform a multivariate analysis of the variance of repeated measures, adjusted by the baseline value of each variable. Any interaction between the primary and secondary endpoints with the group (IG vs CG) and Cohen *d* will be estimated.

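### Centre is left out of the outcome models of a 5-site trial: no bias and no type I error inflation, but a modest and avoidable loss of precision if centres differ in change from baseline

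*Protocol article*

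**What the plan says.** Section 2.1 of the protocol article states the design: "This is a randomized, multicentre clinical trial with 2 parallel groups". The coordinating unit "will coordinate the project on 5 sites from the Network for Preventive Activity and Health Promotion", and these sites lie in five cities.

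Section 2.4 says of allocation: "Participants will be randomly assigned to either the IG or the CG". A computer-generated, concealed sequence is described. Neither stratification nor blocking by centre is mentioned.

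Section 2.9 names the covariates. Changes from baseline are compared "using ANCOVA at 3 and 12 months, adjusting for baseline measures of each variable", and the follow-up analysis is a "multivariate analysis of the variance of repeated measures, adjusted by the baseline value of each variable". Both models name the baseline value and nothing else, and no other section puts centre into a model.

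Section 2.6.7 sends IL-1β, IL-7 and adiponectin to a centralized laboratory. It then lists other blood and urine determinations and says: "The analyses will be performed at the hospitals in the cities participating in external quality assurance programs". That sentence appears to cover the other determinations.

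**The concern.** Centre is known for every participant before randomization. In this trial it can plausibly be related to outcome, because counselling, training in the application and measurement take place in person in five cities. The laboratory determinations not done centrally may also carry some between-hospital variation.

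A model with group and baseline value only leaves any centre differences in change from baseline in the residual error. It also leaves chance differences between the arms in centre mix in the sampling variability of the estimate. Both can be reduced without recruiting anyone, and section 2.3 plans for only 80% power.

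The consequence depends on how allocation was done:
- **Not stratified by centre:** the reported standard error is valid but larger than it need be.
- **Stratified by centre:** the true sampling variance is already reduced, and a model without centre fails to show it, so its standard errors are too large.

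**Working it through.** **Inputs from the protocol article.** Section 2.3: α 0.05 (taken as two-sided), power 80%, SD 12 kg, difference 3 kg, 15% loss to follow-up, 592 participants (296 per group). Section 2.1: 5 sites. **Assumed:** ICCs of 0.01, 0.02 and 0.05, meaning the share of outcome variance that lies between centres.

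**The plan's own figure.** n per arm = 2 × 12² × (1.960 + 0.842)² / 3² = 251.2. Dividing by 0.85 gives 295.5, so 296 per group and 592 in total. The stated sample size is reproduced. Expected completers are 592 × 0.85 = 503.2, or 251.6 per arm.

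**Effect of adding centre.** With centre in the model the residual SD is 12 × √(1 − ICC). The standard error (SE) of the difference is that SD × √(2/251.6). Power is Φ(3/SE − 1.960). The equivalent gain in completers is 503 × ICC/(1 − ICC).

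| ICC (assumed) | Residual SD (kg) | SE (kg) | Power | Equivalent extra completers |
|---|---|---|---|---|
| centre omitted | 12.00 | 1.070 | 80.1% | – |
| 0.01 | 11.94 | 1.065 | 80.5% | 5 |
| 0.02 | 11.88 | 1.059 | 80.9% | 10 |
| 0.05 | 11.70 | 1.043 | 82.0% | 26 |

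The last column depends only on the ICC and the number of completers, not on the 12 kg.

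**Is the analysis without centre valid?** A simulation used 503 completers, 5 centres, allocation not stratified by centre, and 4,000 replicates per setting. The baseline covariate was not simulated. ICCs were 0.01, 0.05 and, as a stress test only, 0.10. With centre omitted:
- the mean estimate was −3.00 to −3.01 kg for a true −3 kg;
- the type I error was 4.4% to 5.0%;
- the model SE of 1.07 kg matched the empirical SE of 1.05 to 1.08 kg.

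**Cost of fitting centre.** Without stratification, group is slightly correlated with centre by chance. Four centre terms inflate the variance of the group effect by roughly 4/502 = 0.8%. At ICC 0.01 the variance ratio is then about 0.99 × 1.008 = 0.998, so almost nothing is gained. The simulation agrees:
- at ICC 0.01 the model SE goes from 1.069 to 1.068 kg, and power is 79.9% without centre and 79.8% with it;
- at ICC 0.05 the SE goes from 1.070 to 1.047 kg, and power from 80.6% to 82.0%.

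The table's gains are therefore slightly optimistic if allocation was unstratified.

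**If allocation was stratified by centre.** The SE from a model without centre is too large by a factor of about 1/√(1 − ICC): 1.005, 1.010 and 1.026 at the three ICCs. The test is then conservative.

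**The case against.** The strongest reply is that nothing here is wrong. Baseline-adjusted ANCOVA under individual randomization is valid without centre, and the ordinary standard error already covers chance imbalance. This stands. A reader might infer that centre imbalance biases the effect or inflates the type I error; neither the document nor the simulation supports that.

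The second reply is that the gain is small and rests on assumed ICCs. This also stands. The figures apply the ICC to the full 12 kg SD, whereas the model analyses change from baseline adjusted for the baseline value. A stable site offset, including a constant offset between hospital laboratories, is largely removed already. Only centre differences in change matter. For the same reason a large ICC for locally assayed outcomes should not be presumed.

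Third, some tempting premises are not in the text:
- **Nurses differing by site** is a reasonable inference but is not stated. The different nurse in section 2.5 concerns the extra intervention-group appointments.
- **Site-specific equipment** has no support. Sections 2.6.1 to 2.6.3 and 2.6.6 name one device or model per measure for the whole trial, and weight is taken on a named scale after calibration.
- **Local laboratories** can concern only the determinations not done centrally. The three named pro-inflammatory markers are measured centrally.

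Fourth, a journal article condenses the full protocol, and a full analysis plan could include centre. This holds for the allocation method, where no mention of stratification does not show that there was none. It has less force for the models, because section 2.9 states what they adjust for and centre is not included.

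**Conclusion.** The point holds as a minor matter of precision. The article states models adjusted only for the baseline value in a 5-site trial. Adding centre would raise power from about 80.1% to between 80.5% and 82.0% at assumed ICCs of 0.01 to 0.05, worth about 5 to 26 of roughly 503 completers. Near ICC 0.01 with unstratified allocation the net gain is practically nil; at 0.05 it is a little under 2 percentage points.

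This rests on four assumptions: the ICCs, which the document does not give; the 12 kg SD and 15% loss from section 2.3; the ICC reflecting centre differences in change rather than stable offsets; and centre effects that act alike in both arms. The planned test is valid as it stands. The point would weigh more if allocation was in fact stratified by centre, because the standard errors would then be overstated as well, by about 0.5% to 2.6% over the same range.

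**What to change.** In section 2.9, add centre (5 levels, fixed effect) to the ANCOVA at 3 and 12 months and to the repeated-measures model, for the primary and secondary outcomes. Include centre in the multiple-imputation model planned in section 2.8.1, so that the imputation and analysis models agree. State in section 2.4 whether allocation was stratified by centre, since that decides whether the adjustment is optional or needed for correct standard errors.

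The change is one phrase in section 2.9, uses a variable already held for everyone, and costs four degrees of freedom out of roughly 500. It should be fixed before the allocation is revealed to the analyst.

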### Analysis of effect by adherence

2.10

To assess the effect of adherence to the application, we will divide the IG into high adherence (≥2 months), and low adherence (<2 months), according to the specified criteria, and the same analysis as previously described will be performed.

### Analysis by subgroups

2.11

The impact of the intervention could be also affected by age, cultural and socioeconomic level, and certain diseases, which will all be analyzed by specific subgroups as previously described. An analysis will be performed to assess differences between men and women for adherence to the application and results in the short term (3 months) and long term (12 months).

### Secondary analysis

2.12

A multivariate analysis of multiple linear regressions will be performed to identify the variables that most influence changes in weight, physical activity, sedentarism, and arterial stiffness.

Continuous information, nutrition, and physical activity, over the 3 months of use of the application and the Smartband, will be collected in the IG. Data will be grouped by week to observe their evolution and compare the changes in these parameters with changes in the main variables (body weight, physical activity, and arterial stiffness).

All statistical analyses will be performed with SPSS version 23.0 (IBM Corp, Armonk, NY), with the level of statistical significance set at *P* ≤.05.

### Ethics and dissemination

2.13

The study was approved by the Clinical Research Ethics Committee of the Health Area of Salamanca (“CREC of Health Area of Salamanca”) in April 2016. In addition, the study was approved by the Ethics Committees of the 4 collaborating centres (CEIC de Aragón [CEICA], CEIC de Castilla la Mancha, CEIC de Baleares and CEIC de Area de Salud de Valladolid Oeste). A SPIRIT checklist is available for this protocol. The trial has been registered in ClinicalTrials.gov with identifier NCT03175614.

Participants must sign the informed consent before inclusion in the study in accordance with the Declaration of Helsinki. Subjects will be informed about the objectives of the study and the risks and benefits of the examinations that they will undergo, including sample collection. None of the testing could result in life-threatening risks for the subjects. Subject confidentiality will be ensured at all times in accordance with current laws and regulations on personal data protection (LOPD 15/1999 of 13 December 1999) as well as the conditions described in Act 14/2007 on biomedical research.

## Discussion

3

The studies available that quantify the effect of smartphone applications (mHealth) on weight loss are increasing. There is a great diversity in the applications used obtaining different results on lifestyle improvement. These mHealth interventions have small to moderate effects on physical activity and sedentary behavior.^[61]^ Recent evidence suggests that applications must include a detailed registration of foods, goals, and customizable challenges and also incorporate personalized feedback and recommendations.^[62]^ Finally, the populations studied are not homogeneous, and therefore generate different results depending on age, sex, and morbidities. Therefore, it is expected that the results of this study will further our understanding of the efficacy of new technologies, combined with traditional counselling, towards reducing obesity and enabling healthier lifestyles.

### Methodological limitations

3.1

Because of the nature of the intervention, participating subjects cannot be blinded. However, towards achieving the greatest possible blinding effect, neither the person performing the statistical analysis nor the person measuring study variables will know to which group each participant belongs. Even though the analysis of some of the results regarding the modification of lifestyle will be performed using self-reported data, validated tools will be used. However, objective data, such as accelerometer for physical activity and weight and body composition measurement, will compliment subjective results. Any difficulties involved in the use of the application may result in an increase in the number of dropouts from the IG.

### Dissemination plan

3.2

We will use a variety of methods to ensure that our work will achieve maximum visibility. The publication of our study protocol provides an important first step in this direction. In this paper, we have sought to offer a comprehensive overview of relevant literature while underlining current research gaps that necessitated the design and implementation of the EVIDENT 3 study. The study results, given their applicability and implications for the general population, will be disseminated in investigator meetings and in articles published in peer-reviewed scientific journals. Minimally, one manuscript is planned for publication with main findings and sub-analyses (in Supplementary Material) and one manuscript for the secondary findings. In addition, a proposal for a doctoral thesis based on this project has been made.
